## Abstract

**Background:**

The progression and complications of chronic kidney disease should differ depending on the cause (C), glomerular filtration rate category (G), and albuminuria (A). The KNOW-CKD (KoreaN Cohort Study for Outcome in Patients With Chronic Kidney Disease), which is a prospective cohort study, enrolls subjects with chronic kidney disease stages 1 to 5 (predialysis).

**Methods/Design:**

Nine nephrology centers in major university hospitals throughout Korea will enroll approximately 2,450 adults with chronic kidney disease over a 5-year period from 2011 to 2015. The participating individuals will be monitored for approximately 10 years until death or until end-stage renal disease occurs. The subjects will be classified into subgroups based on the following specific causes of chronic kidney disease: glomerulonephritis, diabetic nephropathy, hypertensive nephropathy, polycystic kidney disease, and others. The eligible subjects will be evaluated at baseline for socio-demographic information, detailed personal/family history, office BP, quality of life, and health behaviors. After enrollment in the study, thorough assessments, including laboratory tests, cardiac evaluation and radiologic imaging, will be performed according to the standardized protocol. The biospecimen samples will be collected regularly. A renal event is defined by >50% decrease in estimated GFR (eGFR) from the baseline values, doubling of serum creatinine, or end-stage renal disease. The primary composite outcome consists of renal events, cardiovascular events, and death. As of September 2013, 1,470 adult chronic kidney disease subjects were enrolled in the study, including 543 subjects with glomerulonephritis, 317 with diabetic nephropathy, 294 with hypertensive nephropathy and 249 with polycystic kidney disease.

**Discussion:**

As the first large-scale chronic kidney disease cohort study to be established and maintained longitudinally for up to 10 years, the KNOW-CKD will help to clarify the natural course, complication profiles, and risk factors of Asian populations with chronic kidney disease.

**Trial registration:**

No. NCT01630486 at http://www.clinicaltrials.gov.

## Background

Chronic kidney disease (CKD) is a rapidly growing disease worldwide. The prevalence of CKD in Korea is estimated to be 13% in the adult population [1]. Approximately 5% of the Korean adult population is estimated to have decreased renal function with an estimated glomerular filtration rate (eGFR) less than 60 ml/min per 1.73 m^2^[1]. CKD, which leads to dialysis or kidney transplantation, presents a major threat to cardiovascular (CV) events and all-cause mortality [2,3]. A patient with CKD is more likely to die of CV disease than to start renal replacement therapy.

Since 2002, a large number of epidemiologic studies, in addition to the general population, have demonstrated a significantly increased risk of adverse consequences in subjects with albuminuria, even in the presence of normal or mildly decreased GFR [4,5]. This finding warrants a broader view of the early stages of CKD within the nephrology population to determine the variables associated with CKD and the increased risks of death and adverse outcomes [6]. However, the mechanistic link between albuminuria and adverse consequences has not been established.

Kidney Disease: Improving Global Outcomes (KDIGO) 2012 Clinical Practice Guideline for the Evaluation and Management of CKD recommends a new classification of CKD, based on the cause, GFR category, and albuminuria (CGA) [7]. The characteristics of CKD differ significantly depending on the underlying disease or the location of the pathologic-anatomic abnormalities. Therefore, we hypothesized that the progression and complications of CKD should be different among the disease subgroups, which cause CKD. A new perspective in the viewpoint of the “CGA” paradigm is required to analyze and interpret the various parameters associated with CKD.

Nevertheless, recently established CKD cohort studies [8-11] are primarily based on the CKD population with low GFR (less than 60 ml/min per 1.73 m^2^). The above studies targeted the cardiovascular complications from subjects with moderate or severe renal impairment. In these studies, the early stages of renal injury are excluded from their target population and the specific causes of CKD are not considered. In contrast, a new CKD cohort study, including all of the stages of the pre-dialysis CKD population and considering the specific causes of CKD, may lead us to gain insight into understanding the natural progression of CKD and the association between CKD and CV outcomes or mortality.

The KNOW-CKD (KoreaN Cohort Study for Outcome in Patients With Chronic Kidney Disease), funded by the Korea Centers for Disease Control and Prevention (KCDC), was established in 2011 by a group of nephrologists, epidemiologists, biostatisticians, and clinical pathologists in Korea.

The goals of the KNOW-CKD are as follows: 1) to establish an adult pre-dialysis CKD cohort covering the early stages of CKD, as well as the advanced stages of CKD, 2) to investigate the natural history of CKD, such as renal progression, death, and complications with respect to the CGA categories, 3) to evaluate the etiologic factors for renal progression and related complications, 4) to identify the mechanistic link between renal injury and adverse outcomes, and 5) to identify the genetic and molecular influences on renal progression and complications.

In the present paper, we report our study design and methods and results from study participants registered from 2011 to 2013.

## Methods/Design

### Organization

The KNOW-CKD is a patient-based cohort study. Nephrologists working in nine clinical centers in the major university-affiliated hospitals and epidemiologists, pathologists and biostatisticians in a research modulating center are participating in this study. The basic protocol of the study was approved by the ethical committee of each participating center including Institutional Review Boards of Seoul National University Hospital, Severance Hospital, Kangbuk Samsung Medical Center, Seoul St. Mary’s Hospital, Gil Hospital, Eulji General Hospital, Chonnam National University Hospital and Pusan Paik Hospital. Among the nine clinical centers, six centers are located in the metropolitan city of Seoul, one in a satellite area of Seoul, Gyeonggi-do (a province), and two in the southern area of Korea (i.e., Chonnam-do and Busan). Throughout the national health care system, Korea has 44 tertiary-care general hospitals. The distribution of our participating clinical centers is parallel to the distribution of the major hospitals in Korea. The study is supervised by the CKD Advisory Committee, which comprises members from the KCDC and the Korean Society of Nephrology (KSN) (NCT01630486 at http://www.clinicaltrials.gov).

### Study population

Each participating center will enroll approximately 250 consecutive individuals over a 5-year period from 2011 until 2015, totaling 2,450 adult patients with CKD who provide written informed consent. The participating individuals will be monitored for approximately 10 years until death or until ESRD occurs.

The KNOW-CKD will enroll ethnic Korean patients with CKD who range in age between 20 years and 75 years. The CKD stages from 1 to 5 (predialysis), based on the eGFR, is calculated using the four-variable Modification of Diet in Renal Disease (MDRD) equation as follows:

eGFR (ml/min per 1.73 m^2^) = 175 × [serum Cr (mg/dl)] ^-1.154^ × [age]^-0.203^ × [0.742 if female] × [1.212 if black], using serum creatinine concentrations measured at a central laboratory and an assay traceable to the international reference material [12].

Excluded subjects are those who 1) are unable or unwilling to give written consent, 2) have previously received chronic dialysis or organ transplantation, 3) have heart failure (NYHA class 3 or 4) or liver cirrhosis (Child-Pugh class 2 or 3), 4) have a past or current history of malignancy, 5) are currently pregnant, or 6) have a single kidney due to trauma or kidney donation.

We defined and allocated the specific causes of the CKD into four subgroups: glomerulonephritis (GN), diabetic nephropathy (DN), hypertensive nephropathy (HTN), and polycystic kidney disease (PKD). The definition of the subgroup is defined by the pathologic diagnosis, in the event that the biopsy result is available. Otherwise, the subgroup classification depends on the clinical diagnosis. GN is defined by the presence of glomerular hematuria or albuminuria with or without an underlying systemic disease causing glomerulonephritis. The diagnosis of DN is based on albuminuria in a subject with type 2 diabetes mellitus and the presence of diabetic retinopathy. HTN is defined by the patient’s hypertension history and the absence of a systemic illness associated with renal damage. Unified ultrasound criteria [13] will be used to diagnose PKD. The other causative diseases will be categorized as ‘unclassified’.

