### Outcome variables

A renal event is defined by a >50% decrease in eGFR from the baseline values, doubling of serum creatinine, or ESRD. The estimated GFR for defining renal outcome will be based on the four-variable MDRD formula. However, the Chronic Kidney Disease Epidemiology Collaboration (CKD-EPI) creatinine equation [14] or the CKD-EPI creatinine-cystatin C equation [15] will also be employed to estimate GFR.

At each visit, the subjects will be queried and evaluated for CV events, including myocardial infarction (fatal and nonfatal), coronary revascularization, stroke and new onset or aggravation of congestive heart failure. The causes of death will be verified and classified as cardiac, non-cardiac and unknown. An independent committee will adjudicate all of the primary outcomes. The subjects who withdraw from the study will be traced for this type of information with the help of the National Health Insurance System and Korea Statistical Information Service. The secondary outcomes are hospitalization, fracture, QOL, and economic status during the follow-up.

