### Follow-up

The participating subjects will visit the center according to the follow-up schedule. At each visit, the subjects will undergo scheduled tests; the investigators will review the subjects’ recent medical histories and occurrence of events. We assumed that 10% of the individuals would withdraw from the study and that ESRD or death would develop subsequently in 10% of the subjects annually [18]. Efforts will be made to prevent drop-outs, i.e., providing free medical examinations, frequent telephone calls and dietary education.

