### Statistical methods and plan

The baseline characteristics of the study participants for each subgroup were presented with descriptive statistics using a one-way analysis of variance or Kruskal-Wallis test according to the distribution of continuous variables and a chi-square test or Fisher’s exact test for categorical variables.

To analyze the association of outcome variables, the time-to-event analysis will be used to evaluate primary outcomes, such as renal events (initiation of renal replacement therapy and 50% decline of GFR), CV events (myocardial infarction and ischemic stroke) and death. The Kaplan-Meier curves and the proportional hazard models will serve as major statistical methods for the outcomes. The incidence or mortality rates according to each outcome variable will be calculated for each etiologic group; the incidence ratios will be presented with reference to the diabetic nephropathy subgroup. The effect of exposure on the development of outcomes will be analyzed separately in each group and in the overall groups. The heterogeneity of each relative risk within the KNOW-CKD subcohort will be analyzed using the Cochran Q test or using a shared-frailty model, where time-dependent confounders should be adjusted [19]. The CKD progression will be evaluated using decreased GFR calculations. Because it is common for a patient with CKD to have a non-linear decline in GFR or a prolonged period of non-progression [20], we will assess the longitudinal trajectory of GFR for the individual participants of KNOW-CKD using the Bayesian smoothing technique [21]. If the progression of CKD is steady and linear, the generalized estimating equation will be adopted to compare the slope of the GFR with repeated measurements. The progression of CKD will be supplemented with an event-based analysis, whereby the occurrence of ESRD or the substantial decrease of GFR will be treated as the events of interest.

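### Monitoring ends at ESRD with no stated tracing afterwards, so deaths and CV events after ESRD are lost to component analyses that need them; the primary composite is unaffected

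*Protocol article*

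**What the plan says.** All references are to the protocol article.

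- **End of follow-up** (Study population; the Abstract agrees): "The participating individuals will be monitored for approximately 10 years until death or until ESRD occurs".
- **Composite** (Abstract, Methods/Design): "The primary composite outcome consists of renal events, cardiovascular events, and death".
- **Renal event** (Outcome variables): "A renal event is defined by a >50% decrease in eGFR from the baseline values, doubling of serum creatinine, or ESRD". ESRD is therefore itself an event in the composite.
- **Tracing** (Outcome variables): "The subjects who withdraw from the study will be traced for this type of information", using national insurance and statistics sources. Nothing similar is said for subjects whose monitoring stops at ESRD.
- **Planning rate** (Follow-up): a 10% withdrawal assumption and, as a separate item, that "ESRD or death would develop subsequently in 10% of the subjects annually".
- **Analysis** (Statistical methods and plan): renal events, CV events and death are each listed for time-to-event analysis. "The Kaplan-Meier curves and the proportional hazard models will serve as major statistical methods for the outcomes". Further, "The incidence or mortality rates according to each outcome variable will be calculated for each etiologic group", with ratios taken against diabetic nephropathy (DN).
- **Aims** (Background, second goal): the natural history of CKD, which expressly includes death and complications.

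**The concern.** The rule that ends follow-up suits the composite but not all of its components. Once a subject reaches ESRD, a later myocardial infarction, stroke or death has no stated route into the data. ESRD then acts as a censoring event for death and CV events, and it is unlikely to be independent of them. The Discussion cites an adjusted hazard ratio for death of 3.2 at an eGFR of 15-29, so patients close to ESRD do not share the mortality of those far from it.

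The loss is also unlikely to be even across the groups the study sets out to compare. DN starts with by far the largest share of subjects in stages 4-5 and should reach ESRD fastest. At stake are the absolute 10-year risks of death and CV events by cause of CKD, and how far the second goal can be met. A separate SAP could add an estimator, but it cannot recover events that were never collected.

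**Working it through.** The article gives no cumulative risk for any component, so there is no stated figure to reproduce. The only documented rate is the 10% per year. Everything marked *assumed* is not in the article. Constant hazards over T = 10 years are used throughout, and withdrawals are left out.

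**1. Exits through ESRD or death**

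1 − 0.9^10 = 0.651. The equivalent hazard is −ln(0.9) = 0.105 per year. Mean time observed is 0.651/0.105 = 6.2 of 10 years.

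**2. Unevenness by cause** (stages 4 plus 5, Table 2)

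- DN: (121 + 46)/317 = 52.7%
- HTN: (95 + 21)/294 = 39.5%
- GN: (93 + 31)/543 = 22.8%
- PKD: (30 + 12)/249 = 16.9%

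This is baseline stage, not an ESRD rate. It makes uneven exits probable without measuring them.

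**3. Deaths missed**

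*Assumed* death hazard before ESRD d = 0.02. The rest of the plan's 0.105 is ESRD: e = 0.085. *Assumed* death hazard after ESRD is m·d, with m = 1, 2 or 4.

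- Death seen before ESRD: d/(d+e) × (1 − exp(−(d+e)T)) = 0.02/0.105 × 0.651 = 12.4%.
- Kaplan-Meier censored at ESRD: 1 − exp(−0.02 × 10) = 18.1%.
- Total 10-year death: 1 − exp(−(d+e)T) − e·exp(−mdT) × (1 − exp(−(d+e−md)T))/(d+e−md).

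| m | Total death | Kaplan-Meier | Share of deaths missed |
|---|---|---|---|
| 1 | 18.1% | 18.1% | 32% |
| 2 | 23.1% | 18.1% | 47% |
| 4 | 31.3% | 18.1% | 60% |

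The missed share is 1 − 12.4%/total. With the death hazard kept at 0.02, it is 13-33% if ESRD runs at 0.03 per year and 52-78% if it runs at 0.18.

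**4. CV event before ESRD or death**

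*Assumed* CV hazard h = 0.02; competing hazard c for ESRD or death.

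- 1 − KM = 1 − exp(−hT) = 18.1%, whatever c is.
- Cumulative incidence = h/(h+c) × (1 − exp(−(h+c)T)).

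| c per year | Cumulative incidence | Ratio of 1 − KM to it |
|---|---|---|
| 0.03 (*assumed*) | 15.7% | 1.15 |
| 0.105 (plan's 10%) | 11.4% | 1.59 |
| 0.20 (*assumed*) | 8.1% | 2.24 |

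At c = 0.105 the ratio hardly depends on h (1.60 at h = 0.01, 1.58 at 0.03). Two causes with the same CV hazard but exits at 0.03 and 0.20 would show the same Kaplan-Meier curve, while their incidences differ almost twofold (15.7% against 8.1%).

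**5. What remains once ESRD no longer ends follow-up**

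Only death then competes. If ESRD is half to four fifths of exits (*assumed*), the death hazard is 0.053 to 0.021. Cumulative incidence is then 14.2% to 16.4%, and the ratio falls to 1.28 to 1.10.

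**The case against.** The best defence has five parts.

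- **Scope.** The first goal describes a pre-dialysis cohort, so pre-ESRD outcomes might be all that is intended. This has weight, but the second goal names death and complications without that limit, and the analysis section lists death as an outcome in its own right. The boundary should at least be stated.
- **Rates and Cox models.** A reader might infer that every incidence ratio against DN is biased because DN loses most events. The documents do not support this. Events and person-time stop together at ESRD, so person-time ratios and proportional hazards estimates remain interpretable as cause-specific, pre-ESRD quantities. This part of the defence stands.
- **Direction.** A reader might infer that all cumulative risks are overstated. That holds only for 1 − KM read as the risk of an event before ESRD. For total mortality there is no bias if risk is unchanged by ESRD, and understatement if it rises.
- **Composite.** It includes ESRD, so time to first event is unaffected. This stands too.
- **Left to the SAP.** Choosing a competing-risk estimator is commonly left to an analysis plan, and its absence from a condensed article is no fault in itself. Ascertainment is different, because the article fixes when monitoring ends and whom the linkage covers.

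One could also read ESRD exits as withdrawals and so already traced. The Follow-up section counts withdrawal separately from ESRD or death, so that reading is not secure.

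**Conclusion.** The point holds for ascertainment after ESRD and for absolute risks of the components. It should be fixed, but it does not threaten the primary composite.

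Followed as written, the plan loses deaths and CV events after ESRD in a cohort where about 65% are expected to reach ESRD or die within 10 years. Under the assumed hazards, about a third to three fifths of 10-year deaths would be missed. Censored Kaplan-Meier would understate total mortality by 5 to 13 percentage points if mortality after ESRD is 2 to 4 times the earlier rate. For CV events before ESRD or death, 1 − KM would overstate the risk 1.15- to 2.24-fold, depending on how fast subjects exit.

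Only the 10% per year comes from the article. The CV hazard, the split between ESRD and death, and mortality after ESRD are assumptions. A difference between causes is inferred from baseline stage. The 1.6-fold figure should not be quoted as the gain from changing the estimator alone, since it falls to about 1.1-1.3 once follow-up continues past ESRD.

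**What to change.** 1. **Ascertainment (the essential change).** Count ESRD as the renal event, but do not let it end ascertainment of death and CV events. Extend the national insurance and statistics tracing already planned for withdrawals to subjects who reach ESRD, up to year 10.
2. **Estimation (secondary).** Where absolute risks of renal or CV components are shown, use Aalen-Johansen cumulative incidence with death as a competing event, and ESRD as well when the target is pre-ESRD CV risk. Keep Kaplan-Meier for the composite and, once step 1 is in place, for all-cause death.
3. **Labelling.** Mark any estimate that stops at ESRD, including rates and hazard ratios, as pre-ESRD.

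The cost is revised wording, a wider request on a linkage already foreseen, and a check that consent covers it. No visits are added. The consent check is easiest while enrolment, planned to run until 2015, is still open.

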### Data collection

The detailed protocol for data and sample collection is described in Table 1. The eligible subjects will be screened and evaluated at baseline for socio-demographic information, smoking, alcohol consumption, medication, and detailed personal and family medical histories. The anthropometric measurements (height, weight, and waist/hip ratios), and measurements of the resting blood pressure (BP) in the clinic and pulse pressure using an electronic sphygmomanometer will be conducted. The subjects will complete questionnaires concerning quality of life, socio-economic status, educational level, physical activity, health behaviors, and health care facility utilization. After enrollment in the study, the laboratory tests, cardiac evaluation and radiologic imaging will be performed according to the specific protocol. DNA, serum and urine samples will be initially collected. Serum and urine samples will be subsequently collected on a regular basis according to the standardized protocol. The details regarding the study visit and test schedule are shown in Table 1.

**Table 1 T1:** Schedule of the KNOW-CKD at each visit

**Parameter**	**Visit time (year)**												
	**Screening**	**Baseline**	**0.5**	**1**	**2**	**3**	**4**	**5**	**6**	**7**	**8**	**9**	**10**
Informed consent	O												
Demographic information	O												
Medical History	O												
Eligibility confirmation	O												
Recent events			O	O	O	O	O	O	O	O	O	O	O
Medications		O	O	O	O	O	O	O	O	O	O	O	O
Health Questionnaires		O						O					
KDQOL questionnaires		O						O					
Blood pressure		O	O	O	O	O	O	O	O	O	O	O	O
Anthropometry		O	O	O	O	O	O	O	O	O	O	O	O
CBC, chemistry		O	O	O	O	O	O	O	O	O	O	O	O
IDMS-traceable Cr, MDRD eGFR		O	O	O	O	O	O	O	O	O	O	O	O
Cystatin C		O	O	O	O	O	O	O	O	O	O	O	O
HbA1c (diabetic subjects)		O	O	O	O	O	O	O	O	O	O	O	O
Lipid panel, CRP, iron profile		O		O		O		O		O		O	
Intact PTH, 25D, 1,25 D, cardiac troponin T		O		O		O		O		O		O	
Urinalysis		O	O	O	O	O	O	O	O	O	O	O	O
24-h urine collection		O				O		O		O		O	
Electrolyte/Cr/osmolality, albumin/protein (Spot urine)		O		O		O		O		O		O	
Electrocardiogram, chest X ray		O			O		O		O		O		O
Echocardiography, Pulse wave velocity, Ankle-brachial index, MDCT, LS spine lateral X-ray for vascular calcification		O					O				O		
Bone mineral density		O					O				O		O
DNA sample		O											
Plasma/urine sample		O	O	O	O	O	O	O	O	O	O	O	O
Fundus exam (diabetic subjects)		O											
Abdomen CT or MRI (polycystic kidney disease)		O			O		O		O		O		O
Family screen (polycystic kidney disease)		O											

CBC, complete blood count; KDQOL, Kidney Disease –Quality of Life; IDMS-serum cr, serum creatinine measurement using IDMS-traceable method; MDCT, multidetector computed tomography for coronary calcium score.

All of the data, including clinical information, laboratory results and outcome, will be entered into a web-based, electronic, case-reporting form (eCRF). The electronic data management system for the KNOW-CKD was developed by the division of data management in Seoul National University Medical Research Collaborating Center.

